### Adverse events

This is a non-drug intervention trial, using interventions that are within current recommended exercise guidelines, and might be offered as part of a routine clinical service. As such, the risk of severe or unexpected adverse events is low. Dementia is progressive and both cognition and function may deteriorate in the course of the study. Comorbidity and inter-current illness will be very common. A balance must be drawn between ensuring the safety of participants, and failing to identify specific risks amidst numerous reports of un-related incidents.

Falls, injuries, hospital admissions and deaths will be ascertained prospectively as part of the trial outcomes. They will be recorded through diaries, supported by telephone calls from (blinded) researchers where necessary, and by examining electronic health records.

We will define an adverse event as an incident, injury or symptom related to therapy sessions, or exercise undertaken independently. The most likely adverse events are fatigue, minor musculo-skeletal symptoms or injuries such as muscle stiffness, or sprains, or increased falls though increased activity. Some conditions such as arthritis or angina may be exacerbated by exercise. Adverse events will be monitored by therapists and RSWs, and reported where they occur. However, this will give a biased impression of prevalence, as the different treatment arms have substantially different amounts of contact with professional staff. Medical judgement will be exercised in deciding whether an adverse event is serious, expected or causally-related.

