### Follow-up

Researchers will visit participants at home at 12 months (± 2 weeks) to complete health status assessments by interview with the participant and informant. Participants will keep a daily diary for 12 months, detailing activities and exercises undertaken and recording falls. This will be supported and prompted by monthly telephone calls [98]. Measures will be taken to ensure that falls ascertainment is not biased across the intervention arms (e.g. therapists or RSWs will be asked not to prompt recall of falls). Health and social care use will be ascertained during the telephone calls, using electronic healthcare records and the Client Service Receipt Inventory (CSRI) at follow-up interview. Persistence with the therapy programme, health and social care use, and hospitalisation will be ascertained by short questionnaire at 18 and 24 months.

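### Non-injury symptoms reach the record only through therapists and support workers, whose contact differs widely by arm; a neutral question on the existing blinded monthly calls would cheaply reduce this admitted bias

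*Protocol article*

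**What the plan says.** The Adverse events section of the protocol article sets up two routes for harms.

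The first covers four outcomes in every arm: "Falls, injuries, hospital admissions and deaths will be ascertained prospectively as part of the trial outcomes". Their sources follow: "They will be recorded through diaries, supported by telephone calls from (blinded) researchers where necessary, and by examining electronic health records".

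The second covers adverse events as the plan defines them: "We will define an adverse event as an incident, injury or symptom related to therapy sessions, or exercise undertaken independently". Capture rests on treating staff: "Adverse events will be monitored by therapists and RSWs, and reported where they occur". The section then comments on its own method: "However, this will give a biased impression of prevalence, as the different treatment arms have substantially different amounts of contact with professional staff". It closes with a later assessment: "Medical judgement will be exercised in deciding whether an adverse event is serious, expected or causally-related".

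The Follow-up section describes a daily diary kept for 12 months and adds: "This will be supported and prompted by monthly telephone calls". It limits those calls to no arm. The Blinding section says that staff who collect data by telephone do not know the allocation.

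**The concern.** Two features act together on the second route. Relatedness is a condition of entry, so a symptom that the therapist does not link to exercise never reaches the later judgement of causality. That judgement can only remove events. The chance of being noticed also depends on how often staff visit, which the design varies on purpose between arms.

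For falls, the Follow-up section promises measures to keep ascertainment even across arms. Nothing comparable is stated for symptoms.

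At stake is how far symptom burden can inform the choice between supervision levels. The Discussion says that this choice, or how to tailor supervision, depends on many factors. The Aim section lists intervention burden, study procedures and data collection among the things to be tested. A symptom record that mainly follows visit numbers adds little to any of these.

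**Working it through.** **Inputs** (Intervention section unless stated)
- High-intensity arm: 51 sessions in total. These comprise 11 from registered therapists, plus support-worker visits twice weekly, weekly, fortnightly and monthly for 3 months each.
- Moderate-intensity arm: 11 sessions, all within 12 weeks.
- Control arm: a falls assessment and up to two follow-up visits. Taking the assessment as one visit (an assumption), this is 1 to 3.
- Calls: monthly for 12 months in all arms (Follow-up), by blinded staff (Blinding).

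**Step 1. The plan's own total of 51.** With w weeks per quarter, support-worker visits are 2w + w + w/2 + 3.
- w = 12: 24 + 12 + 6 + 3 = 45, and 45 + 11 = 56.
- w = 13: 26 + 13 + 6.5 + 3 = 48.5, and 48.5 + 11 = 59.5.

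Plain addition does not give 51. The section says that some visits are joint. Counting each joint visit once gives 51 if 5 are joint (56 − 51) or about 8.5 are (59.5 − 51). The number of joint visits is not given, so 51 can be reconciled but not confirmed. I use 51 below.

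**Step 2. Contact ratios.**

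| Comparison | Calculation | Ratio |
|---|---|---|
| High to moderate | 51/11 | 4.6 |
| High to control, 1 visit | 51/1 | 51 |
| High to control, 2 visits | 51/2 | 25.5 |
| High to control, 3 visits | 51/3 | 17 |
| Moderate to control | 11/1 to 11/3 | 11 to 3.7 |

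**Step 3. Timing.** Moderate-arm participants are taught to carry on after supervision ends, and the definition includes independent exercise. Over a year, 52 − 12 = 40 weeks, about nine months, have no scheduled visit at which a qualifying symptom could be reported. The high-intensity arm has scheduled visits throughout, though less often as supervision tapers.

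**Step 4. Which harms are exposed.**
- Falls, injuries, admissions and deaths: diary, blinded calls and records in all arms. Sprains may be caught here as injuries.
- Fatigue, stiffness and worsening arthritis or angina short of admission: no stated route except therapists and support workers. A symptom that leads to a health-care contact may leave a trace in the service-use data, but is not recorded there as an adverse event.

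**Step 5. The alternative.** If symptoms were asked about on the monthly calls, each arm would have 12 planned contacts, a ratio of 12/12 = 1.

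**The case against.** The strongest reply is that the choice is reasoned. The Adverse events section notes that comorbidity and intercurrent illness will be very common, and weighs safety against losing specific risks among many unrelated reports. It therefore sends the more objective harms to all-arm ascertainment and uses therapist reports for monitoring. It also warns readers not to take those reports as prevalence. This stands, and it is why I do not propose removing relatedness from the whole definition.

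Second, the Feasibility analysis and Efficacy analysis sections state no comparison of adverse events between arms, and the trial has 60 participants with no formal sample size. A reader might infer that a planned safety analysis is invalid. The documents do not support that, since no such analysis is described.

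Third, a reader might infer that symptom counts will differ 17- to 51-fold. That would need reporting in proportion to visits. One visit can pick up what happened since the last, and the figure of 51 applies only to a control participant with no follow-up visit.

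Fourth, a reader might infer that the control arm cannot record an event. The definition includes independent exercise and does not expressly tie it to the prescribed programme, so that goes too far.

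Fifth, the phrase "supported by telephone calls from (blinded) researchers where necessary" might be read as making the calls conditional. The Follow-up section plainly makes them monthly, and the phrase can mean that calls supplement the diary. This is a matter of wording, not a conflict in design.

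Finally, a symptom question could lead participants to mention therapy to a blinded caller. That risk is real but small if the question is fixed and neutral.

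**Conclusion.** The point holds as a cheap improvement confined to non-injury symptoms. For these, the only stated channel has 51, 11 and about 1 to 3 planned contacts by arm, and none in the moderate arm for about nine months. The plan admits the resulting bias and offers no remedy, although an even, blinded channel already exists. The ratios of 4.6 (high to moderate) and 17 to 51 (high to control) are ceilings on unequal ascertainment. No reporting rate is given from which to estimate the actual imbalance.

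This rests on the stated total of 51 sessions, on counting the control assessment as one visit, and on the monthly calls running in all arms for 12 months.

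Two wider readings are tempting. One is that harms in general are unevenly captured. The all-arm ascertainment of falls, injuries, admissions and deaths rules that out. The other is that the definitive trial will inherit the problem. Nothing says that this procedure carries over, and the study exists to adapt procedures first.

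**What to change.** - Add a short, fixed symptom question to the existing monthly blinded call in all three arms. It should not mention therapy or exercise, and callers should repeat the request not to reveal the treatment group.
- Record the answers whatever the cause, and judge relatedness afterwards. Use only these call-based data for any description of symptoms by arm.
- Keep therapist and support-worker reports for monitoring under the present definition. List them separately, per visit made.
- Change the conditional phrase about calls in the Adverse events section so that it matches the monthly calls in the Follow-up section.

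The calls are already planned: at most 60 × 12 = 720 across the trial. The cost is a slightly longer call, more unrelated minor symptoms to log and assess, and a small risk of unblinding callers. A short, fixed question limits the logging burden that the plan is right to worry about, and the control arm's answers supply the background rate against which an exercise-related symptom could be seen.

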### Data management

Data management will be according to the Standard Operating Procedures of NWORTH CTU. Quantitative data will be entered into a MACRO database, written and maintained by NWORTH CTU, by research assistants. This incorporates range checks at the point of data entry. Data will be further checked by the study statistician, and a sample verified against source documents. Qualitative (audio-and video-recorded) data will be transcribed and anonymised, and managed using NVivo 11 software (QSR International, Daresbury, UK). The research grant co-applicants will have access to the final dataset. Paper records will be securely archived according to University of Nottingham standard operating procedures.

### Statistics and data analysis

#### Feasibility analysis

The main analysis will be of feasibility outcomes. We will calculate:Recruitment rate (randomisations per month)Retention rate (proportion completing therapy programme and study follow-up)Therapy adherence rate (proportion of professionally-supervised visits undertaken, and time spent doing self-directed therapeutic exercise or activity)Missing data (proportion fully completed, for each scale, at each time point).

Participant throughput and flow will be summarised for each trial arm using a CONSORT diagram. Reasons for non-eligibility, non-treatment, withdrawals and non-completion of questionnaires will be reported.

#### Efficacy analysis

Descriptive statistics (e.g. means, medians, proportions, standard deviations and ranges) of baseline demographic, health status and service use data will be calculated for each trial treatment arm.

We will compare changes in health status outcomes between the three trial arms.

The Disability Assessment for Dementia and Nottingham Extended ADL scale outcomes will be compared using an analysis of covariance to adjust for the baseline score and stratifying variables. The nature of the distribution of the falls data will also be examined to determine how best to analyse the falls data in the main trial. Statistical analysis will be performed on an intention-to-treat basis. There will be no imputing of missing data. Assumptions in determining the sample size of the main trial will be checked.

#### Qualitative analysis

Data will be coded and a thematic analysis undertaken using the principles of constant comparison [107, 108]. A separate coding frame will be developed for each dataset after which themes from each will be systematically compared. Each coding frame will be developed through the independent coding of about five transcripts and associated field notes by at least three researchers. Iterative comparison and discussion will continue until the coding frame has stabilised. Subsequent transcripts will be coded by a research fellow, with 10% double-coded to establish consistency and increase comprehensiveness. Coding will incorporate a priori topics of relevance to the study; for example: ‘understanding of dementia’, ‘relevance of exercise’, ‘motivation’, ‘burden’, ‘comorbidity’ and others identified inductively from the data.

Coding proceeds through three stages. Open coding (indexing of sections of text/video themes to ‘nodes’); detailed scrutiny of the content of each node (‘coding on’) when coding is refined through reorganisation and reallocation into subnodes, and regrouping of nodes and subnodes into a hierarchical structure (‘tree’); relating sub-nodes to overarching core themes. Each data set will be subject to both separate and integrated analysis. Findings will be synthesised through charting and matrix displays.

#### Process evaluation

We will follow MRC guidance (2014) [73] on process evaluation, which describes three components using a mixed-methods approach: implementation or delivery; mechanisms of impact; contextual factors.

Implementation (delivery of intervention), includes fidelity (quality of delivery) and dose (quantity of delivery). Records of therapy sessions undertaken and self-directed activity will be examined, and video-recorded therapy sessions will be assessed qualitatively for fidelity. Mechanisms of impact and contextual factors include engagement and adherence. These will be investigated through the qualitative studies.

We will also do a qualitative analysis of 10 purposively-selected video-recorded intervention sessions, which will be transcribed and analysed. Sessions will be selected to include a range of professionals, patient participants and stages of intervention delivery. We will use these to derive insight into: intervention delivery in real world settings; its consistency; interactions between patient, carer and professional participants; patient and carer responses and engagement with the intervention; the circumstances and contextual factors influencing engagement; models of best practice in delivering the intervention.

#### Optimising uptake and adherence

Using the Capability, Opportunity, Motivation – Behaviour (COM-B) framework [58], we will seek evidence on what support participants would like, or will need, to achieve short- and long-term adherence. We will review methods to support uptake and adherence in exercise interventions reported in the literature, drawn from a variety of conditions, which might be adapted or used for people with dementia. We will develop a strategy for promoting and supporting uptake, adherence and persistence with the intervention, develop guidance on tailoring, need for direct supervision, and describe habit formation and factors that predict successful adherence.

We will analyse baseline distributions, changes and associations with psychological variables hypothesised to determine motivation and adherence, including motivation of participants to exercise (BREQ-2 [102]), and basic psychological needs, [105], and clinician factors, including communication style [100]), work motivation [106], and basic psychological needs [105].

#### Economic analysis

Preliminary cost-effectiveness analysis will be undertaken from a National Health Service and personal social services (public sector multi-agency) perspective with short-term time horizon relating to the trial follow-up period. Cost-effectiveness analysis will be conducted in line with NICE guidelines for technical appraisal [109] and MRC guidelines for the evaluation of complex interventions [110]. A primary cost-effectiveness analysis will be undertaken on cost per point improvement on the Disability Assessment for Dementia scale. A secondary cost-effectiveness analysis will be undertaken on the cost per fall averted. A cost-utility analysis will be undertaken using EQ-5D-3 L and DEMQoL as sources of utility weights for calculating quality adjusted life years (QALYs) [111, 112]. Data from the feasibility study will be used to model longer-term costs and benefits to estimate potential lifetime savings to the NHS and social care of an observed improvement in ADL. Deterministic and probabilistic sensitivity analysis will be undertaken. Social Return on Investment (SROI) analysis will be undertaken and a SROI ratio will be generated from the total value of inputs and total value of outputs [113, 114]. The resulting ratio will be the amount of social value generated for every £1 invested in the programme.

Sensitivity analysis will be conducted to vary the costs of inputs (e.g. the cost of the staff delivering the programme), and to vary the discount rate applied (base case rate of 3.5%, sensitivity analysis rate of 1.5%) in accordance with NICE guidelines [115].

### Governance

An independent Programme Steering Committee and Data Monitoring Committee have been constituted, each with an independent chair, expert clinician, statistician and (on the steering committee) patient and public contributor. The Trial sponsor is Nottingham University Hospitals NHS Trust.

## Discussion

There is a pressing need for interventions to maintain activity and independence among people with dementia. This is to enable people to ‘live well’, to help prevent crises, and to mitigate the increasing burden on health and social care of dementia-related dependency. Intervening at an early stage may enable people to establish new health habits before the inevitable progression of dementia. Fall-related injury and activity restriction are often responsible for deterioration, or a ‘spiral of decline’. Falls prevention for older people in general is well-established, but this has not yet been adapted for people with dementia.

We present the protocol of a complex study, aiming both to establish the feasibility of conducting a large RCT of an exercise intervention for people with early dementia, and to optimise implementation of the intervention so that the RCT will evaluate an intervention that is practical, well-justified and suitable for wider-scale subsequent adoption.

The development and evaluation of complex interventions is a methodological challenge [73, 110]. Our stance is that if an intervention is suitable for testing on a randomised basis, then an RCT is the best method to use. Other methodologies, such as realist evaluation, may also contribute to understanding complex interventions. The embedding of a process evaluation and work to study engagement and adherence, will allow us to answer questions about ‘what works, for whom, under what circumstances and why?’ [116].

Several conditions need to be met for an RCT to be successful. In common with all RCTs, we must establish research feasibility: recruitment rates, data collection, follow-up and the properties of outcome measures. But for complex interventions, it is also necessary that the intervention tested is deliverable and optimised. RCTs are expensive and labour-intensive; adequate preparatory work is required to ensure that the intervention is fit for testing, and sufficiently well-defined to be repeatable. For applied health research that anticipates early patient benefit, the intervention should be suitable for widespread adoption in health care services if the results are favourable.

Our study is designed to examine whether these conditions are satisfied, and to enable adjustment or adaptation in the light of experience. Our intervention is based upon work we have conducted over several years examining, and contributing towards, a wide body of physiological evidence that links exercise to improved outcomes [19, 55, 57, 92–94]. The feasibility RCT examines two variants of the exercise intervention with higher and lower degrees of supervision, on the basis that a lower intensity support intervention would be less expensive to deliver, but might not ensure the long-term adherence presumed necessary for benefits to be seen, whilst more intensive supervision will be more expensive but may be more effective [34–36, 48, 57]. The decision to choose one arm or the other, or how to tailor supervision according to individual circumstances, in a subsequent large RCT will depend upon many factors, critically including the degree to which long-term adherence is established. This will be informed by the process evaluation, and motivation and adherence study. Given that both intervention arms will incur health care costs, it is necessary to demonstrate whether there is a reasonable likelihood of health gains before conducting a large and expensive RCT, and any subsequent health benefit justifies the costs of the intervention. Economic appraisal towards the end-of-life is contentious, ideally requiring an approach which can model costs and benefits over the whole remaining lifespan, and adopting a wider frame of reference than cost per QALY alone. For this reason we are undertaking preliminary economic analyses, including Markov modelling and social return on investment analyses.

We face several methodological challenges. Research involving people with dementia can be difficult, even when impairments are mild. However, we have expertise in doing such studies. We note that people with dementia and their families are keen to be involved in research. The provisions of the English Mental Capacity Act are designed to enable inclusion, and our governance processes ensure that studies are conducted ethically. Many studies have demonstrated that people with dementia can be successfully recruited to trials, and useful and valid patient-centred outcomes can be measured. The recording of falls and levels of activity will be challenging, and will be examined in this study.

The studies described represent part of a research programme aimed at understanding activity-limitation among people with dementia, how to intervene to promote activity and reduce falls, and how to get such a therapy programme to work in practice. The protocol describes work on the final stages of developing the intervention, preparing a definite RCT, and data for economic modelling.

The definitive RCT is due to recruit from September 2018 and complete in 2021.

